### Statistical methods

The intention to treat principle will be adhered to, where clusters will be analysed according to their time of switching between control and HfLI. Randomisation is conducted as soon as all communities have provided support of the HfL Initiative in their community and prior to the commencement in any of the participating communities. Unblinding of the communities allocated to the next 6-monthly cross-over date will be done 6 months prior to that cross-over date, to allow for a lead-in phase of community preparation that is still the control period. To allow for delays in implementation, a separate per protocol analysis will be performed with the assessments now placed into one of the three categories: control period pre-allocated cross-over date (including the lead-in period of 6 months), post-allocated cross-over date but pre-implementation (the training phase) and post-implementation (from commencement of employment and including integration phase). The distribution of results across the control group will be compared with the HfLI group

Characteristics of individuals and clusters in the HfLI will be summarised by their exposure status [29]. Demographic characteristics of children will be summarised as proportions and/or means (SD) or medians (IQR) by control and HfLI group. For a sub-set of the population, risk factor questionnaires with parents will be used to examine the distribution of known confounders (such as birth weight, smoke exposure from pre-conception, breast feeding, household crowding, etc.) between control and HfLI periods.

#### Primary outcome

The primary outcome is the proportion of children who receive an ear assessment (diagnosis) within 6 months. A multilevel mixed-effects generalised linear model will be used. This will involve fitting a binomial regression model with fixed effect for HfLI status and time as a categorical variable and a random intercept for cluster and coefficient for time to account for both within—and between—period intra-cluster correlations [27]. Estimates of treatment effect will be presented as odds ratios and the 95% confidence interval using a logit link function.

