We acknowledge the difficulties of the SW-CRT design, including having to adjust for calendar time, as systematically more assessments are accrued later under intervention condition than under control conditions. It is also possible that the effect of the Ear Health Facilitator may vary over the duration of the study. The open cohort allows for continuous entry, and as the only participant inclusion criteria is age 0 to 16 years, the risk of selection bias is low. Adjustment for repeat measures (6-monthly surveillance and follow-up ear assessments) has been accounted for in sample size and analysis plan.

Our trial incorporates a co-design approach to implementation, led by Community Reference Groups, and a strengths-based approach that respects the cultural, linguistic and relationship knowledge of community members.

The comparator (control periods) represents standard care. To maintain interest and communication with communities during the control period, we will offer annual 1-day workshops for resident health service staff in the prevention, diagnosis and management of OM. Such brief workshops have always been available to services and will not contaminate our outcome measure. We also anticipate little impact of within cluster contamination.

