#### Sample size

Sample size for the SW-CRT is 18 communities, each having at least 100 children 0 to 16 years of age. The sample size calculation is based on the proportion of participants who receive an ear assessment during the study period. The method of sample size calculation for a cohort SW-CRT design [27] was adapted using numerical simulation. Current evidence suggests that about 33% of children under 5 years of age received a completed ear assessment between 2011 and 2016 in the Northern Territory [11]. We would assume an absolute increase of 10% in the proportion of children who receive an ear assessment to be feasible and clinically important. Given a control proportion of 0.329 and an absolute difference of 0.1 using a two-sided test at 5% level of significance, our sample size of average 90 children per cluster (community) per 6 month period will achieve a total sample size of 1620 at 98% power assuming an intra-cluster correlation coefficient (ICC) of 0.06, a cluster auto-correlation coefficient (CAC) of 0.7 and individual autocorrelation (IAC) due to repeated measurement of children receiving ear diagnoses. We conducted sensitivity analysis using different effect sizes, power, ICC and CAC scenarios to determine if our required number of clusters will be adequate for our study. The result indicates that across a range of ICCs (0.02–1), CAC (0.6–0.8), baseline proportions (0.23–0.53) and effect sizes (0.10–0.20) our sample size of 18 clusters (communities) and 5 step lengths will achieve over 80% power to detect absolute increases between 10% and 20%. In the unlikely event of communities withdrawing, our sensitivity analysis shows that we will still have adequate power assuming we end up with 16 communities, allowing for withdrawal of two communities [28].

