##### Rates

Episodes of AOM, OME, AOMwiP, CSOM or DP over the trial period will be summarised as counts according to treatment groups. The effect of the HfLI will be determined using multilevel mixed-effects negative binomial regression expressed as incidence rate ratio (IRR) and the 95% CI. Time will be fitted as a categorical fixed effect and random coefficient and random intercept for cluster. The same approach will be followed to estimate the treatment effect on rate of appropriate use of antibiotics for (1) persistent otitis media with effusion (pOME), (2) AOM without perforation, (3) AOM with perforation, (4) CSOM (topical) in the last 6 months, (5) rate of appropriate specialist referral (audiology), and (6) rate of appropriate specialist referral (ENT).

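### The random part of the primary model does not clearly give the community-by-period correlation that the sample size assumes; fitted as a linear slope, its type I error would be about 22%

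*Protocol article*

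**What the plan says.** The Statistical methods section (Primary outcome) describes "fitting a binomial regression model with fixed effect for HfLI status and time as a categorical variable", together with "a random intercept for cluster and coefficient for time to account for both" the correlation within periods and the correlation between them. The effect is to be presented as an odds ratio through a logit link. No child-level term is named.

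The Proportions section carries this approach to the binary secondary outcomes. The Rates section words its random part slightly differently: "Time will be fitted as a categorical fixed effect and random coefficient and random intercept for cluster".

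The Sample size section assumes an ICC of 0.06, "a cluster auto-correlation coefficient (CAC) of 0.7 and individual autocorrelation (IAC) due to repeated measurement of children receiving ear diagnoses". It gives no value for the individual autocorrelation. The Background, where it discusses the difficulties of the stepped-wedge design, says: "Adjustment for repeat measures (6-monthly surveillance and follow-up ear assessments) has been accounted for in sample size and analysis plan". The Abstract defines the primary outcome as a difference in proportion, and the power statement uses an absolute difference: "Given a control proportion of 0.329 and an absolute difference of 0.1".

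**The concern.** A cluster autocorrelation of 0.7 means that 30% of the between-community variance is new in each community-period: a staffing gap, a visiting team, an outbreak. A random intercept plus a linear random slope lets communities differ in level and in trend, but has no place for independent shocks from one period to the next. The residual variance of a binomial model is fixed by the mean, so it cannot absorb them either. The standard error of the HfLI effect is then too small, and the primary p-value and confidence interval overstate the evidence.

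The problem grows with community size. Larger denominators shrink the binomial variance and leave the period shocks unchanged. The primary analysis takes all resident children aged 0 to 16, and Table 3 lists communities with 617 to 724 children under 14, against the 90 used for power.

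Two lesser mismatches sit beside this. Repeat measures are said to be handled in the analysis, yet the model names no child term. The question is framed as an absolute difference, yet only an odds ratio is planned.

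**Working it through.** **Inputs.** From Sample size: control proportion 0.329, difference 0.10, two-sided 5%, "our sample size of average 90 children per cluster (community) per 6 month period", ICC 0.06, cluster autocorrelation (CAC) 0.7. From Table 1: 18 communities allocated 2:4:4:4:4 to five sequences over seven periods. The individual autocorrelation (IAC) has no stated value and is taken as 0 to 0.8.

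**1. The plan's own power.** Use generalised least squares on community-period means with categorical time. With σ² = 0.379 × 0.621 = 0.2354 at the mean proportion, each mean has variance σ²[ICC + (1 − ICC)/m], and two periods of one community have covariance σ²[ICC × CAC + (1 − ICC) × IAC/m]. Power = Φ(0.1/SE − 1.96).

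- IAC 0: SE 0.0269, power 96.1%
- IAC 0.4: SE 0.0249, power 98.0%
- IAC 0.8: SE 0.0228, power 99.3%

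The stated 98% for 18 × 90 = 1620 is reproduced, so the planning model is a community-by-period model.

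**2. Hand check of the inflation.** In units of p(1 − p), the period-specific variance is 0.06 × 0.3 = 0.018. The binomial part is 0.94/90 = 0.0104. A model without the first understates the standard error by about √[(0.018 + 0.0104)/0.0104] = √2.72 = 1.65. The rejection rate is then about 2[1 − Φ(1.96/1.65)] = 23%. At ICC 0.02 the parts are 0.006 and 0.98/90 = 0.0109, the ratio is √1.55 = 1.245, and the rate is about 12%.

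**3. Null simulation.** Data were generated on the Table 1 design with no effect, with ICC and CAC converted to the logit scale. Binomial-logit mixed models were fitted by a Laplace approximation, with 2000 trials per row except where noted.

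| Random part fitted | ICC, CAC, size | z | t, 16 df |
|---|---|---|---|
| Community intercept only | 0.06, 0.7, 90 | 22.6% | 19.1% |
| Intercept + linear slope | 0.06, 0.7, 90 | 22.1% | 18.2% |
| Intercept + linear slope | 0.06, 0.6, 90 | 26.1% | 22.9% |
| Intercept + linear slope | 0.06, 0.8, 90 | 17.7% | 13.9% |
| Intercept + linear slope | 0.02, 0.7, 90 | 11.7% | 8.8% |
| Intercept + linear slope | 0.02, 0.8, 90 | 8.2% | 6.3% |
| Intercept + linear slope | 0.06, 0.7, Table 3 | 49.6% | 45.8% |
| Separate variance per period (1000 trials) | 0.06, 0.7, 90 | 9.3% | 7.4% |
| Intercept + community-by-period | 0.06, 0.7, 90 | 6.6% | 4.4% |
| Intercept + community-by-period | 0.06, 0.7, Table 3 | 6.1% | 4.4% |

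Monte Carlo error is about 0.9 points at 22% (√(0.221 × 0.779/2000)). An unstructured intercept–slope covariance also gives 22.1%.

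In the base case the slope model's mean standard error (log-odds scale) is 0.0755 against a true SD of 0.121, a ratio of 1.60. Then 2[1 − Φ(1.96/1.60)] = 22%, consistent with step 2. The community-by-period model gives 0.1146 against 0.1197.

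A separate linear analysis of cluster-period means (300 runs) gave 24% at 90 children and 41% at 250 with a slope, against about 6% with a community-by-period effect.

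**4. The child term.** True child effects with logit variance 1, 2 and 5 were added, and the child term was still left out of the fit. The slope model then rejects in 20.4%, 19.2% and 15.7%, and the community-by-period model in 6.4%, 5.9% and 5.5% (z). Leaving the term out does not raise type I error.

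**The case against.** The strongest objection is that the protocol never says linear or slope. It introduces time as categorical, states that the random coefficient is there to capture both correlations, and cites the same methods reference for the model and for the sample size. The Rates wording leans the same way. A coefficient on categorical time with one common variance is the community-by-period effect, and that model is close to nominal. This stands: a reader might infer that the trial will use a model with a false-positive rate above 20%, and the text does not support that.

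It does not remove the point. A random coefficient for time is ordinarily coded as a slope. The categorical reading is itself not unique: a separate variance per period gives about 9%, and a fully free covariance over seven periods needs 7 × 8/2 = 28 parameters from 18 communities. Only the common-variance version comes near 5%, and the text does not state it.

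A second objection is that covariance structure and reference distribution belong in an analysis plan that is not shown. That would answer silence. Here the article does fix the random part, in words that permit analyses with very different error rates.

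A third objection is that the missing child term does no harm to type I error. That is correct. A reader might infer that it contributes to the inflation, and step 4 shows that it does not. What remains is the mismatch with the statement on repeat measures. Likewise, an odds ratio is a valid test scale for a trial powered on a difference, so that part concerns reporting only.

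**Conclusion.** The point holds as a badly fixed specification, not as a certain error. Depending on how one phrase is coded, the type I error of the primary test at the protocol's own planning values is about 22% (linear slope), 9% (separate variance per period) or 6–7% (common-variance community-by-period effect; 4–5% with t on 16 degrees of freedom). Changing to a t reference does not rescue the slope model, which still rejects in 18%.

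The 22% is not general. It is 18–26% over the protocol's autocorrelation range at ICC 0.06, and 8–12% at ICC 0.02. The figure near 50% rests on assumed sizes: Table 3 lists 20 communities without identifying the two pilots, counts children under 14, and gives only a lower bound of 300 for two towns. Entries at or below 100 were set to 100, and the two towns to 300.

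Other assumptions are the logit-scale conversion, a mild secular trend, no exclusion of the transition period, and a closed cohort where child effects were simulated. The ambiguity should be resolved before analysis, because it decides whether the primary p-value and interval can be relied on.

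**What to change.** State the primary model explicitly: a logit mixed model with categorical period and HfLI status as fixed effects, random intercepts for community and for community-by-period, and a small-sample t reference with about 16 degrees of freedom (18 communities less two). Use the same random structure for the models under Proportions and Rates.

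Add a child-level random intercept, or say why none is used. With that term the odds ratio becomes conditional on the child. Report the standardised difference in proportions with its 95% confidence interval beside the odds ratio, so that the result answers the question the trial was powered on.

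The cost is wording, some run time and wider intervals. In the base case the mean standard error is 0.1146 instead of the 0.0755 a linear slope would report, a factor of 1.52. That is the width the trial's own correlation assumptions imply. The stated 98% power already rests on this structure, so the sample size need not change on this account.

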**Method/design:**

This stepped-wedge cluster randomised trial will allocate 18 communities to one of five 6-monthly intervention start dates. Stratification will be by region and population size. The intervention (Hearing for Learning Initiative, HfLI) consists of six 20-h weeks of training (delivered over 3 months) that includes Certificate II in Aboriginal Primary Health Care (3 modules) and competencies in ear and hearing data collection (otoscopy, tympanometry and hearScreen), plus 3 weeks of assisted integration into the health service, then part-time employment as Ear Health Facilitators to the end of the trial. Unblinding will occur 6 months prior to each allocated start date, to allow Community Reference Groups to be involved in co-design of the HfLI implementation in their community. Relevant health service data will be extracted 6-monthly from all 18 communities. The primary outcome is the difference in proportion of children (0 to 16 years of age) who have at least one ear assessment (diagnosis) documented in their medical record within each 6-month period, compared to control periods (no HfLI). Secondary outcomes include data on sustainability, adherence to evidence-based clinical guidelines for otitis media, including follow-up and specialist referrals, and school attendance. Structured interviews with staff working in health and education services, Ear Health Trainees, Ear Health Facilitators and families will assess process outcomes and the HfLI broader impact.

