#### Employment phase

Service delivery (Table 4). Briefly, the Ear Health Facilitator(s) will obtain informed consent for ear and hearing surveillance of at least 100 children every 6 months. Otoscopy, tympanometry and hearScreen findings will be entered into the child’s electronic health record (PCIS or Communicare). A diagnosis and care plan will be made in consultation with the child’s doctor, nurse or Aboriginal health practitioner. The Ear Health Facilitator will assist with implementation of the care plan with the family. The Ear Health Facilitator will support families and children to improve school attendance and support teachers who have children in their class who need ear or hearing assistance.

Ear Health Facilitators who resign or lose their job will not be replaced. If there is more than one Ear Health Facilitator employed in the community (i.e. job sharing), the remaining employee will be offered a higher full time equivalent. Alternatively, the health service may employ an Ear Health Trainee who successfully completed the Cert II and clinical competency training; however, the service must deliver the integration phase according to the HfLI protocols. The health service will be reimbursed by the HfLI for employment of the Ear Health Facilitator(s) until the end of the project.

Regular 6-monthly 1-day refresher training workshops for Ear Health Facilitators will be a part of the HfLI program during the employment phase. Sustainability will be measured.

We do not anticipate discontinuing or modifying the HfLI. An independent Data Safety and Monitoring Board (iDSMB) will review progress of the trial. The terms of reference will include stopping rules regarding safety concerns. The HfLI will cease in a community if the Community Reference Group, the Local Authority and the community health and education services request this in writing (i.e. participant withdrawal). Communities will not be replaced.

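### The primary effect is planned only as a single constant odds ratio, which gives neither the absolute difference the trial is powered on nor, if the effect varies, its average over HfLI periods

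*Protocol article*

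**What the plan says.** Three places in the protocol article set the scale of the effect.

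- Abstract, Method/design: "The primary outcome is the difference in proportion of children (0 to 16 years of age) who have at least one ear assessment (diagnosis"), with HfLI periods compared with control periods.
- Sample size: "We would assume an absolute increase of 10% in the proportion of children who receive an ear assessment to be feasible and clinically important". The calculation follows suit: "Given a control proportion of 0.329 and an absolute difference of 0.1".
- Statistical methods, Primary outcome: "Estimates of treatment effect will be presented as odds ratios and the 95% confidence interval using a logit link function". The model is a binomial mixed model with one fixed effect for HfLI status, time as a categorical variable, a random intercept for community and a random coefficient for time.

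Two places bear on whether the effect is constant.

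- The introduction, in its discussion of the design: "It is also possible that the effect of the Ear Health Facilitator may vary over the duration of the study".
- Employment phase: "Ear Health Facilitators who resign or lose their job will not be replaced". The same paragraph then allows a remaining job-sharer more hours, or the hiring of another qualified trainee.

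The participant timeline counts the 3-month integration phase as intervention time. A sensitivity analysis with and without integration is planned.

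**The concern.** There are two gaps between what the trial sets out to learn and what its primary model will report.

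**Scale.** The trial judges importance in absolute points, but an odds ratio becomes points only once a baseline is fixed. The protocol's own sensitivity range for the baseline runs from 0.23 to 0.53. The article also promises observed proportions, but these cannot fill the gap. In a stepped wedge HfLI time falls later than control time, and the introduction itself says that calendar time must be adjusted for.

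**Averaging.** A single HfLI term is naturally read as the average effect over HfLI time. In a stepped wedge with categorical time that holds only if the effect is the same in every period since start. If the effect grows or fades, the term is a weighted sum whose weights can be negative, and the headline can lie well below or above the true average.

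At stake is whether a reader can tell if 10 points was reached, and whether a programme with a slow start would look weaker than it was.

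**Working it through.** **Inputs.** From Sample size: control proportion 0.329, difference 0.10, 90 children per community per 6 months, ICC 0.06, CAC 0.7, and "using a two-sided test at 5% level of significance". From Table 1: 18 communities allocated 2:4:4:4:4 over 7 periods. Table 1 has HfLI starting in periods 2 to 6, and Table 2 in TP3 to TP7, so both were computed. No value is given for the individual autocorrelation (IAC); it was taken as 0 to 0.9.

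**Method.** Generalised least squares on community-period means, with period effects and one HfLI term. With total variance σ², the variance is σ²·ICC·CAC for community, σ²·ICC·(1−CAC) for community-period and σ²·(1−ICC) for individuals. The individual part is divided by 90 and split by IAC into a lasting and a period-specific part. Power = Φ(0.10/SE − 1.96).

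**Step 1: the stated power.** With σ² = 0.329 × 0.671 and IAC 0.3, SE = 0.0246 and power is 98.2%. Over IAC 0 to 0.9 and other reasonable choices of σ², power is 96.1% to 99.6% for either table. The stated 98% is reproduced, and 18 × 90 = 1620.

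**Step 2: scale.** OR = (0.429/0.571)/(0.329/0.671) = 0.7513/0.4903 = 1.53.

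- Baseline 0.23: odds 0.2987 × 1.532 = 0.4577, proportion 0.314, gain 8.4 points.
- Baseline 0.53: odds 1.1277 × 1.532 = 1.728, proportion 0.633, gain 10.3 points.

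**Step 3: weights of the single term by HfLI period since start.**

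| Starts | 1 | 2 | 3 | 4 | 5 | 6 |
|---|---|---|---|---|---|---|
| Table 1 | 0.77 | 0.44 | 0.09 | −0.10 | −0.14 | −0.06 |
| Table 2 | 0.77 | 0.33 | 0.05 | −0.09 | −0.06 | none |

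These are for IAC 0.5; over IAC 0 to 0.9 they move by about 0.01. For Table 2, the time period containing training is kept as control. Replacing the community-period component by a random linear slope for time leaves the weights negative from period 4 on.

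**Step 4: what varying effects would give.** With Table 2 starts, the HfLI community-periods by duration number 18, 14, 10, 6 and 2, in all 50. With Table 1 they number 18, 18, 14, 10, 6 and 2, in all 68.

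- *Half effect in the first period, then 10 points.* Estimate: 10 − 5 × 0.77 ≈ 6.1. True average: (18×5 + 32×10)/50 = 8.2 (Table 2), or (18×5 + 50×10)/68 = 8.7 (Table 1).
- *Build-up of 2.5, 5, 7.5, 10, 10 (Table 2).* Estimate: about 2.4. True average: (45+70+75+60+20)/50 = 5.4.
- *Fade of 10, 7.5, 5, 2.5, 0 (Table 2).* Estimate: about 10.2, slightly above the largest effect in any period. True average: (180+105+50+15+0)/50 = 7.0.

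The pattern does not come from the linear approximation. A large-sample logistic fit with fixed community and period effects was run with half the log odds ratio in the first period and an odds ratio of 1.53 afterwards. It gave 1.29, against an average of 1.45 (Table 1) or 1.42 (Table 2).

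**Step 5: precision of an average over time since start.** With one HfLI effect per period since start, averaged over HfLI community-periods, and a true constant 10 points:

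| Analysis | SE, IAC 0 to 0.9 | Power |
|---|---|---|
| Single term, either table | 0.0267 to 0.0221 | 96.3% to 99.5% |
| Average, Table 1 | 0.0376 to 0.0319 | 75.8% to 88.0% |
| Average, Table 2 | 0.0317 to 0.0265 | 88.5% to 96.6% |

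**The case against.** The strongest defence is that an odds ratio from a mixed logistic model is valid and conventional, that the body of the article defines the outcome simply as a proportion, and that a standardised risk difference or an exposure-time analysis is detail a statistical analysis plan may supply. The first part stands: the odds ratio is not wrong as a relative measure. The last would stand if the article were silent. It is not: it names the model and the effect measure, and these do not match its own definition, target and caveat.

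A second defence is that early dilution is already covered by the analysis with and without integration. This helps in part, but that analysis moves the boundary of HfLI time and is not described as giving an average over time since start. The per-protocol analysis deals with delayed implementation, and the interaction with time is tied to subgroup variables.

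Several stronger readings are tempting but unsupported.

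- *That the estimate is almost entirely the first HfLI period.* This needs the whole 6-month period containing training to be dropped. The intention-to-treat text does not say so, half of that period is control time, and dropping it gives power of about 88% (at IAC 0.5), not the stated 98%.
- *That the protocol expects the effect to vary.* It says only that this is possible.
- *That leavers leave a gap for good.* The same paragraph allows partial cover.
- *That the effect must shrink with community size.* The article gives 100 children per 6 months as a minimum and as a target, not as a cap, so no size-dependent effect can be calculated from it.

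**Conclusion.** The point holds. As written, the primary result will not give an adjusted absolute difference, although importance and power are set on that scale. If the effect changes with time since start, the single term will not be its average over HfLI periods. In the mildest case considered, half effect in the first period only, it would report about 6.1 points against 8.2 to 8.7, roughly a quarter to 30% too low.

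This rests on a linear approximation, a nested-exchangeable correlation with the stated ICC and CAC, an assumed IAC, and effect shapes that are illustrative and not forecasts. The exact weights would differ somewhat under the planned logistic model; their pattern would not.

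A reader might infer that the primary test or the 98% power is invalid. It is not: under a constant effect both stand. This is an inexpensive improvement that should be made, not a flaw that undermines the trial.

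**What to change.** 1. From the same primary model, report the adjusted risk difference between HfLI and control with its 95% CI, standardised over resident children, beside the odds ratio. Name that population in the plan, since averaging over communities could give a different figure.
2. Prespecify a supporting analysis with one HfLI effect per time period since start, and report its average over HfLI community-periods with a 95% CI.
3. State which table's start periods define HfLI time, since Tables 1 and 2 differ.

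Cost: wording in the analysis plan, with no new data and no change to the sample size. The exposure-time average is less precise (about 76% to 88% power with Table 1 starts, 88.5% to 97% with Table 2 starts, against 96% to 99.5% for the single term), and the longest duration rests on two communities. It should therefore support the primary test and not replace it.
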